### Adherence and treatment integrity

Data will be collected with respect to participants’ attendance of GET or CBT sessions, dropout from the intervention (<2 sessions attended), and therapists’ adherence to the protocol. Adherence to GET and CBT intervention protocols will be determined by means of evaluating the registration forms completed by therapists, including components of the intervention protocol that have been addressed during each session. In addition, with permission of participants, all CBT sessions will be audio taped and upon study completion a random sample of 5% will be analysed to determine treatment integrity.

### Refusal of study participation and study dropout

The researcher will record the reasons why patients do not participate, why participants dropout from the intervention, and why study assessments are not completed (T1, T2, or T3). Upon completion of the study, these reasons will be categorised, scored and analysed to gain insight into the generalisability of the findings.

### Outcomes

Outcome measures and data collection time points are listed in Table 3. The primary endpoint of this study is the post-intervention assessment (T1), 14 weeks after randomisation. Primary and secondary outcomes will be measured at baseline (T0), post-intervention (T1) and follow-up (T2, T3). Proposed mediators will only be assessed at T0 and T1.

**Table 3 Tab3:** Data collection time point of all outcome measures and proposed mediators

Concept	Questionnaire	Measurement time points			
		T0	T1	T2	T3
Socio-demographics	Self-report questionnaire	X			
Medical characteristics	Medical chart review	X	X		
Primary outcome:					
Fatigue severity	CIS *fatigue severity*	X	X	X	X
Secondary outcomes:					
Fatigue	EORTC QLQ-C30 *fatigue*	X	X	X	X
Quality of life	EORTC QLQ-C30 *global health status*	X	X	X	X
Functional impairments	SIP	X	X	X	X
	EORTC QLQ-C30 *emotional functioning*	X	X	X	X
	EORTC QLQ-C30 *physical functioning*	X	X	X	X
Proposed mediators:					
Physical activity	Actigraphy during 12 consecutive days	X	X		
Physical fitness	6MWT	X	X		
Self-efficacy	SES	X	X		
Fatigue catastrophising	FCS	X	X		

*T0* baseline (pre-intervention), *T1* post-intervention/UC (14 weeks post-randomisation), *T2* first follow-up assessment (18-weeks post-randomisation), *T3* s follow-up assessment (26-weeks post-randomisation)

#### Primary outcome

Fatigue severity will be measured using the subscale *fatigue severity* (8 items, 7-point Likert scale) of the Checklist Individual Strength (CIS-fatigue) [33]. Scores range from 8–56. A score of 35 points or higher is an indication for severe fatigue. The CIS-fatigue has been used in previous intervention studies aimed at CRF and proved to be sensitive to change [23, 27]. The CIS-fatigue has good reliability (Cronbach’s alpha = 0.88) and discriminative validity [37].

#### Secondary outcomes

Fatigue will also be assessed with the symptom scale *fatigue* (3 items, 4-point Likert scale) of the European Organisation for Research and Treatment of Cancer Quality of Life Questionnaire (EORTC QLQ-C30, version 3.0). The EORTC QLQ-C30 is developed for use in clinical trials in cancer patients [38]. This instrument consists of five functional and three symptom scales in addition to a scale on global health related quality of life (HRQoL), and a number of single items assessing additional symptoms [38, 39]. Total scores on each subscale are linearly converted to a 0 to 100 scale. Higher scores represent more fatigue.

The subscale *global health status/QoL* (2 items, 7-point Likert Scale) of the EORTC QLQ-C30 will be used to measure quality of life. A high score indicates good HRQoL. The EORTC QLQ-C30 is one of the most commonly used HRQoL instruments [40] and is known to be a reliable and valid measure of the quality of life of cancer patients [38].

Functional impairments will be assessed with two instruments*.* We will include seven subscales of the Sickness Impact Profile (SIP) to assess the level of functional impairments [41]. This questionnaire measures the influence of complaints in different areas of daily functioning. The following subscales will be used: alertness behaviour, sleep, homemaking, leisure activities, mobility, social interactions, and ambulation. High scores reflect high levels of functional impairments. The SIP is known to be a reliable instrument with sufficient content validity [42]. In addition to the SIP, functional impairments will also be assessed by the subscales *emotional functioning* (4 items, 4-point Likert scale) and *physical functioning* (5 items, 4-point Likert scale, range 0 to 100) of the EORTC QLQ-C30. Raw scores for both subscales are convertible to a score of 0 to 100. A high score represents a high level of functioning.

#### Proposed mediators

Change scores (T1-T0) for each proposed mediator will be calculated and used for multiple mediation analysis. The following proposed mediators will be assessed at T0 and T1:

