### Aims of the TIRED study

We designed a multicentre RCT to test the efficacy of either GET or CBT compared to Usual Care (UC) in reducing fatigue (primary outcome) in incurable cancer patients receiving systemic treatment with palliative intent. In addition, the efficacy on improving quality of life and functional impairment will be studied. All outcomes will be assessed at baseline, and at 14, 18 and 26-weeks post-randomisation. We will assess the efficacy of GET or CBT compared to UC directly post-intervention at 14-weeks post-randomisation, which is the primary endpoint of this study. In addition, we will determine whether the expected intervention effects are sustained at follow-up assessments (18-weeks and 26-weeks post-randomisation). Furthermore, if GET and/or CBT are efficacious in reducing CRF, we will perform a mediation analysis to test if the changes in four variables (i.e., physical activity, physical fitness, self-efficacy with respect to fatigue, and/or fatigue catastrophising) mediate the reduction in fatigue.

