### Statistical analyses

The statistician who will perform data analyses will be blinded for intervention allocation. To test the efficacy of both interventions compared to UC, an ANCOVA will be performed for each intervention with *fatigue severity* (CIS-fatigue) at T1 as dependent measure, condition as fixed factor and CIS-fatigue screening score as covariate [47]. Missing data is a common problem in palliative care research and is also anticipated in our study as a result of deteriorating health or because the patient has died. Data will be primarily analysed on complete case basis, i.e. only data from evaluable participants with a T1 assessment will be used. The *p*-level is adjusted to 0.025 to account for the two primary analyses, i.e., GET versus UC and CBT versus UC. When statistically significant differences between GET versus UC and/or CBT versus UC are found, additional sensitivity analysis accounting for all randomised participants will be done to explore the impact of missing data. Several methods of imputation are available and the choice will depend on the actual circumstances of missing data. We will record the causes of missing data and careful considerations will be given to which imputation procedure should be used.

In addition, ANCOVA will be performed for the secondary outcomes (*fatigue, quality of life, and functional impairments*), with baseline score (T0) on the dependent measure as covariate. In these exploratory analyses a *p*-level of 0.05 will be used. Longer-term follow-up effects at T2 and T3 will also be tested using ANCOVA, with baseline score (T0) on the dependent measure as covariate. Again, in these explorative analyses a *p*-level of 0.05 will be used. No sensitivity analysis will be done, as the power for follow-up analyses will be limited due to the expected significant amount of attrition.

Mediation analysis will be conducted to explore the possible underlying mechanisms of the expected reduction in fatigue severity (CIS-fatigue) brought on by GET and CBT at T1. Following recommendations of Preacher and Hayes (2008) [48], we will perform multiple mediation analysis using bootstrapping to test the mediating effect of four potential mediators (i.e., changes in *physical activity, physical fitness, self-efficacy with respect to fatigue, and catastrophising in response to fatigue*). We will only perform multiple mediation analysis when there is a significant effect of one or both interventions compared to UC.

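### The exploratory mediation analysis uses raw mediator change scores, leaves the form of the fatigue outcome open and omits the baseline mediator; each reading can attenuate the mediator-to-fatigue path or create a false one

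*Protocol article*

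**What the plan says.** Under Proposed mediators, the article fixes the form of the mediator: "Change scores (T1-T0) for each proposed mediator will be calculated and used for multiple mediation analysis". The four mediators are physical activity, the six-minute walk, self-efficacy and fatigue catastrophising. Under Outcomes, "Proposed mediators will only be assessed at T0 and T1".

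Under Statistical analyses, the method is given: "we will perform multiple mediation analysis using bootstrapping to test the mediating effect of four potential mediators". The target of explanation is "the expected reduction in fatigue severity (CIS-fatigue) brought on by GET and CBT at T1". The Aims section says that changes in the four variables are tested to see whether they "fatigue catastrophising) mediate the reduction in fatigue". Neither place says how fatigue enters the model, and no covariate is named for it.

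The same section does name a covariate for every other model. The primary ANCOVA uses the CIS-fatigue screening score, and the secondary and follow-up ANCOVAs are run "with baseline score (T0) on the dependent measure as covariate".

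The analysis is exploratory and conditional: "We will only perform multiple mediation analysis when there is a significant effect of one or both interventions compared to UC".

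**The concern.** A change score M1 - M0 tends to be negatively correlated with M0, and M0 is likely to be related to fatigue at T0. Unless M0 is in the outcome model, the coefficient on the change score mixes the effect of interest with that baseline association. How it mixes depends on what the fatigue outcome is, which the article leaves open.

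At stake is the trial's only planned evidence on how GET or CBT works. A real mediator may be missed, or a variable with no effect on T1 fatigue may be credited with part of the benefit.

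**Working it through.** **The plan's own figures.** The article gives no figure for the mediation analysis. Its sample size reproduces: 51 / (1 - 0.30) = 72.9, so 73 per arm and 219 in total. One intervention against usual care has 2 x 51 = 102 evaluable participants.

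**Assumptions.** Mediator SDs are 1 within arm at T0 and T1, with T0-T1 correlation rho = 0.5 to 0.8. The mediator-to-fatigue path is b = -0.4 and the fatigue SD is 1. A higher mediator value means less fatigue; for catastrophising the signs reverse. None of these values is in the article. It gives one T0-T1 correlation, 0.10, for CIS-fatigue only.

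**Case 1: T1 fatigue depends on the T1 mediator level.** Y0 = b M0 + e0 and Y1 = b M1 + e1, where e0 and e1 correlate 0.1 or 0.5. D = M1 - M0.

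- *Unadjusted T1 level on D.* Slope = b(1 - rho) / [2(1 - rho)] = b/2 = -0.20, for any rho. With unequal SDs, s = SD(M0)/SD(M1), the ratio to b is (1 - rho s)/(1 + s² - 2 rho s). For s = 1.1 and rho = 0.8 this is 0.12/0.45 = 0.27; for s = 0.9 and rho = 0.8 it is 0.28/0.37 = 0.76.
- *T1 level on D and T0 fatigue.* Slope = b(1 + c) / [2 - b²(1 - rho)], where c = b² rho + 0.84 x corr(e0, e1) is the covariance of Y0 and Y1 (0.84 = 1 - b²). For rho = 0.5 and error correlation 0.1: c = 0.08 + 0.084 = 0.164, slope = -0.4 x 1.164/1.92 = -0.24 (39% loss). For rho = 0.8 and error correlation 0.5: c = 0.128 + 0.42 = 0.548, slope = -0.4 x 1.548/1.968 = -0.31 (21% loss).
- *Fatigue change on D.* Y1 - Y0 = b D + (e1 - e0), so slope = b = -0.40. No bias.
- *T1 level on D (or M1), M0 and T0 fatigue.* Slope = b = -0.40. No bias.

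**Case 2: the mediator has no effect on T1 fatigue, but M0 and Y0 are associated within arm** (b0 = -0.4), and Y1 = k Y0 + noise.

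- *Unadjusted T1 level on D.* Slope = -k b0/2 = +0.10 at k = 0.5 and +0.02 at k = 0.1. The sign is opposite to benefit.
- *Fatigue change on D.* Slope = (1 - k) b0/2 = -0.10 at k = 0.5 and -0.18 at k = 0.1. The sign is that of benefit. With an arm effect on the mediator of 0.6 SD, the false indirect effect is -0.06 to -0.11 SD.
- *With T0 fatigue, or with M0 and T0 fatigue.* Slope = 0.

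**Case 3: T1 fatigue follows the mediator change**, Y1 = k Y0 + b D + noise, with b = b0 = -0.5 and k = 0.5. Unadjusted level on D gives -0.5 + 0.125 = -0.375 (25% loss). Change on D gives -0.5 - 0.125 = -0.625 (25% too large). With T0 fatigue, or with M0 as well, the slope is -0.50.

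**What this does at the planned size.** Simulation with one mediator, 51 per arm, percentile bootstrap and an arm effect on the mediator of 0.6 SD, so the true indirect effect in case 1 is 0.6 x -0.4 = -0.24 SD. Ranges cover the assumed correlations and Monte Carlo error.

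| Outcome model | Power, case 1 | Flagged, case 2 |
|---|---|---|
| T1 level on change | 27-50% | 5-17%, nearly all against benefit |
| plus T0 fatigue | 37-83% | about 5% |
| Change on change | 53-88% | 7-26%, towards benefit |
| T0 mediator and T0 fatigue included | 73-95% | 4-6% |

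**The case against.** The strongest objection is that a reader might infer a regression of unadjusted T1 fatigue on mediator change, and so conclude that the plan halves true mediation. The article does not say that. It speaks of a reduction in fatigue, which fits a change score or a baseline-adjusted T1 score at least as well, and every other outcome model in the section carries a baseline covariate. This stands: halving belongs to one reading only, and there only with equal SDs and a level-driven effect.

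A reader might also infer that baseline differences between arms can pass for mediation. Under randomisation such differences are chance. The mechanism is a within-arm association between baseline mediator and baseline fatigue. Under the unadjusted-level reading the false signal runs against benefit, and at a fatigue carry-over of 0.1, in line with the article's own 0.10, the flag rate is nominal (4.6-5.4%).

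Next, covariates of an exploratory model are commonly left to an analysis plan, and change scores do not rule them out: with M0 in the outcome model, M1 and M1 - M0 have the same coefficient. This stands in part. Silence on covariates alone would be no finding. But the article fixes the mediator as a raw change score, and no reading of the outcome makes that safe without the baseline mediator.

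Finally, the analysis is exploratory and runs only after a significant intervention effect, and the simulation has one mediator where the plan enters four jointly. Both limit the weight of the point.

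**Conclusion.** The point holds as a weakness in a stated method for an exploratory analysis. Depending on how the outcome is read, and if T1 fatigue depends on the T1 mediator level, the mediator-to-fatigue path is attenuated by about half (unadjusted T1 fatigue, equal SDs) or by about 20-40% (only T0 fatigue adjusted for). If the effect is change-driven, the loss is 25% in the first of these readings and nil in the second, under the values used. With fatigue change as outcome the path is unbiased when the mediator acts equally at both times, but under no effect it can show a false path of about -0.10 to -0.18 towards benefit. Of the models compared, only the one with the T0 mediator and T0 fatigue was right in all three cases.

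All mediator correlations, SDs and path sizes are assumptions, so the figures show orders of magnitude. The primary comparison, its alpha and the sample size are untouched.

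**What to change.** Under Proposed mediators and Statistical analyses, or in the analysis plan before the data are analysed, state:

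- the mediation outcome is CIS-fatigue at T1;
- mediator models: each T1 mediator on arm, its T0 value and T0 CIS-fatigue;
- outcome model: T1 CIS-fatigue on arm, the four T1 mediators (or, equivalently, their change scores), the four T0 mediators and T0 CIS-fatigue;
- the indirect effects are bootstrapped from these models.

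All T0 values are already collected (Table 3), so no visit, instrument or participant is added, and recruitment is still under way. The cost is a few sentences and up to five baseline covariates (four mediators and fatigue) in the outcome model, with about 102 participants per comparison.

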##### Physical activity

The level of physical activity will be assessed with actigraphy. Participants will be wearing an actometer around the ankle for twelve consecutive days and nights following T0 and T1. This actometer is a motion-sensing device based on a piezo-electric sensor recording the number of movement at five-minute intervals and with highly reproducible readings [43]. The mean daily physical activity score over twelve days can be calculated as a measure of physical activity.

##### Physical fitness

We will assess the level of physical fitness with the Six-Minute Walk Test (6-MWT). This is an easy to perform and practical submaximal exercise test that has been increasingly used across various patient populations. The 6-MWT will be conducted in an indoor corridor on a pre-measured test-course of 20 meters. Participants will be instructed to walk from one end to the other while attempting to cover as much distance as possible during the allotted time. Patients who normally use walking aids will be allowed to use them during the test. The total walking distance covered in six minutes provides an indirect measure of aerobic functional fitness [44].

##### Self-efficacy with respect to fatigue

The seven-item self-efficacy scale (SES) will be used to measure the amount of experienced control over fatigue [26]. All items are scored on a 4-point Likert scale. Higher scores are indicative for more sense of control.

##### Fatigue catastrophising

We will use the ten-item Fatigue Catastrophizing Scale to measure catastrophising in response to fatigue [45]. All items are scored on a 5-point Likert scale. Higher total scores indicate more fatigue catastrophising.

### Sample size calculation

Based on the primary outcome measure of the TIRED study, efficacy of one or both interventions is demonstrated when mean fatigue severity (CIS-fatigue) in participants assigned to GET and/or CBT is significantly lower at T1 compared to participants assigned to UC. A clinically relevant difference between the intervention arms and the UC arm of at least 6 points is expected for the primary outcome (CIS-fatigue). Per arm, a minimum number of 51 evaluable participants at T1 would be needed for a *t*-test with a power of 0.80 and a two-sided alpha of 0.025 (corrected to account for the two comparisons: GET versus UC and CBT versus UC). According to Borm et al. [46], using analysis of covariance (ANCOVA) instead of a *t*-test to analyse treatment effects on a continuous outcome measure (CIS-fatigue) increases the power and reduces the needed sample size in RCTs. This proposed ‘design factor’ for ANCOVA can be calculated by multiplying the number of participants needed for the *t*-test by 1 – *p*
^2^, where *p* is the correlation between the outcome measure at T0 and T1. Since no data on the correlation of the CIS-fatigue from earlier trials in this particular patient group were available, we used a conservative approach by assuming a weak correlation (1 – 0.10^2^ = 0.99) and thus the number of participants needed was not reduced. Anticipating an attrition rate of 30%, we aim to recruit a target sample size of 219 participants at T0 (73 participants per arm).

### Statistical analyses

The statistician who will perform data analyses will be blinded for intervention allocation. To test the efficacy of both interventions compared to UC, an ANCOVA will be performed for each intervention with *fatigue severity* (CIS-fatigue) at T1 as dependent measure, condition as fixed factor and CIS-fatigue screening score as covariate [47]. Missing data is a common problem in palliative care research and is also anticipated in our study as a result of deteriorating health or because the patient has died. Data will be primarily analysed on complete case basis, i.e. only data from evaluable participants with a T1 assessment will be used. The *p*-level is adjusted to 0.025 to account for the two primary analyses, i.e., GET versus UC and CBT versus UC. When statistically significant differences between GET versus UC and/or CBT versus UC are found, additional sensitivity analysis accounting for all randomised participants will be done to explore the impact of missing data. Several methods of imputation are available and the choice will depend on the actual circumstances of missing data. We will record the causes of missing data and careful considerations will be given to which imputation procedure should be used.

In addition, ANCOVA will be performed for the secondary outcomes (*fatigue, quality of life, and functional impairments*), with baseline score (T0) on the dependent measure as covariate. In these exploratory analyses a *p*-level of 0.05 will be used. Longer-term follow-up effects at T2 and T3 will also be tested using ANCOVA, with baseline score (T0) on the dependent measure as covariate. Again, in these explorative analyses a *p*-level of 0.05 will be used. No sensitivity analysis will be done, as the power for follow-up analyses will be limited due to the expected significant amount of attrition.

Mediation analysis will be conducted to explore the possible underlying mechanisms of the expected reduction in fatigue severity (CIS-fatigue) brought on by GET and CBT at T1. Following recommendations of Preacher and Hayes (2008) [48], we will perform multiple mediation analysis using bootstrapping to test the mediating effect of four potential mediators (i.e., changes in *physical activity, physical fitness, self-efficacy with respect to fatigue, and catastrophising in response to fatigue*). We will only perform multiple mediation analysis when there is a significant effect of one or both interventions compared to UC.

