### Procedure

Eligible patients willing to participate in the study will be asked to sign informed consent upon which they will be invited by a research assistant to complete the baseline assessment (T0) at their own hospital. Upon completion of T0, the research assistant will use a central web-based randomisation service to randomly allocate a participant to one of the three study arms: (1) GET in addition to UC; (2) CBT in addition to UC; or (3) control group receiving UC (see Fig. 1). Participants assigned to GET or CBT will start the intervention approximately two weeks after T0. Both interventions will be delivered at or near their own hospital over a period of 12 weeks. Participants assigned to CBT will complete a set of additional questionnaires to determine relevant intervention modules prior to the first intervention session. Participants assigned to GET will complete an additional submaximal test to determine physical fitness during the first intervention session. At 14 weeks, participants are invited by the research assistant to complete the post-intervention assessment (T1) at the hospital. Follow-up assessments at 18 weeks (T2) and 26 weeks (T3) are entirely web-based and will be completed at home. For participants that do not have Internet access, a paper version of the follow-up questionnaires will be send to their home address, which can be returned in a self-addressed, pre-stamped envelope.

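### The primary T1 ANCOVA adjusts for the CIS-fatigue screening score, while the design factor and every other ANCOVA use T0; adjusting for T0 is a free gain in consistency and expected precision

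*Protocol article*

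**What the plan says.** Under Statistical analyses, the primary ANCOVA of CIS-fatigue at T1 has "condition as fixed factor and CIS-fatigue screening score as covariate". A reference is cited at that sentence, but the text gives no reason for preferring the screening score.

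The same section handles the other analyses differently. The secondary outcomes are adjusted for their own T0 score. For follow-up it states: "Longer-term follow-up effects at T2 and T3 will also be tested using ANCOVA, with baseline score (T0) on the dependent measure as covariate". CIS-fatigue is among the follow-up outcomes, since Aims of the TIRED study asks whether the effects are sustained at 18 and 26 weeks and Table 3 schedules CIS-fatigue at T0, T1, T2 and T3.

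Under Sample size calculation, the ANCOVA design factor is one minus the square of a quantity that "is the correlation between the outcome measure at T0 and T1".

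The two scores are separate measurements. Under Recruitment, screening takes place in routine clinic visits, before or during treatment. Written information and two researcher calls one week apart follow. Under Procedure, consent and T0 come next, and then: "Upon completion of T0, the research assistant will use a central web-based randomisation service".

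**The concern.** The confirmatory test takes as its baseline a routine-care eligibility score, although a scheduled research measurement on the same scale is taken just before allocation. Two features make the screening score the weaker predictor of T1:

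- **Age.** It precedes T0 by at least the week between the two calls. The article gives no upper limit for the interval.
- **Restricted range.** Only scores of 35 or more on a scale of 8 to 56 lead to entry, so the spread of the screening score is cut directly. T0 is restricted only through its correlation with screening.

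A weaker covariate leaves more residual variance and a wider confidence interval than the collected data allow. One outcome also gets two baselines, screening at T1 and T0 at T2 and T3, and the correlation that defines the design factor is not the one that the primary model uses.

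**Working it through.** **1. The plan's own figures.** The inputs come from Sample size calculation: "A clinically relevant difference between the intervention arms and the UC arm of at least 6 points is expected"; "a power of 0.80 and a two-sided alpha of 0.025"; "Per arm, a minimum number of 51 evaluable participants at T1 would be needed"; correlation 0.10; attrition 30%.

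- Design factor: 1 − 0.10² = 0.99, and 51 × 0.99 = 50.49, which rounds up to 51.
- Attrition: 51 / 0.70 = 72.9, which rounds up to 73 per arm.
- Total: 3 × 73 = 219, as stated.

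No SD is given, so it is solved from n = 51. The normal approximation gives SD = 6 × √(51/2) / (2.241 + 0.842) = 9.83. The noncentral t gives 9.70.

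**2. Does the covariate affect the sample size?** No. The design takes nothing from ANCOVA, so 51, 73 and 219 hold with either score.

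**3. Power as a function of the covariate.** With n = 51 per arm, a 6-point difference, alpha 0.025 and residual SD = 9.70 × √(1 − ρ²), where ρ is the correlation of the covariate with T1 among trial participants (an assumption):

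| ρ | Power |
|---|---|
| 0.10 | 80.4% |
| 0.20 | 81.7% |
| 0.30 | 83.9% |
| 0.40 | 86.9% |
| 0.50 | 90.6% |

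Power does not fall below the planned 80% at any ρ.

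**4. How much weaker is the screening score?** The documents give no correlation of any kind, so this step rests on assumptions. Screening, T0 and T1 were simulated as trivariate normal with a common mean and SD, limited to 8–56, and kept only if screening was 35 or more. The loss is the ratio of residual variances, (1 − ρ²(screening, T1)) / (1 − ρ²(T0, T1)), after selection. Results for mean 35 and SD 10 before selection:

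| Assumed before selection: screening–T0, screening–T1, T0–T1 | After selection: screening–T1, T0–T1 | Variance ratio |
|---|---|---|
| 0.8, 0.5, 0.6 | 0.32, 0.48 | 1.17 |
| 0.7, 0.4, 0.5 | 0.25, 0.40 | 1.12 |
| 0.6, 0.3, 0.4 | 0.18, 0.33 | 1.09 |
| 0.8, 0.5, 0.5 | 0.32, 0.34 | 1.01 |

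Mean 30 with SD 12, and mean 38 with SD 9, give nearly the same ratios (1.09 to 1.17 in the first three rows, 1.01 to 1.02 in the last).

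The first three rows give T0 a correlation with T1 that is 0.1 higher than that of screening before selection. The last row makes the two equal, so that truncation alone acts. Most of the loss in the first three rows therefore comes from the assumed advantage of T0. A ratio of 1.17 means a standard error about 8% larger (√1.17 = 1.08), and 1.01 means about 0.5%.

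The range of 1% to 17% belongs to these scenarios and is not a bound. With equal correlations of 0.5 and a screening–T0 correlation of 0.6, the excess is about 4% to 6%. If T0 is given a correlation 0.2 higher than screening (0.7, 0.4, 0.6), it is about 31%.

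**The case against.** The strongest reply is that the specified model is valid. The screening score precedes randomisation and is named in advance, so the estimate is unbiased and the type I error is controlled. That stands. Three stronger readings are tempting, and the documents do not support them.

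- **The covariate undermines the sample size.** A reader might infer this because the design factor is defined by T0. But the calculation assumed a correlation of 0.10 and took no reduction, so the mismatch lies in how the covariate is defined and not in the number of participants.
- **Chance imbalance at T0 distorts the result.** Its expectation is zero and the standard error already reflects it. It is the same efficiency loss described in another way.
- **T1 cannot be compared with T2 and T3.** Under randomisation, a linear ANCOVA with either covariate targets the same mean difference from usual care at each time point. The article specifies no formal comparison between time points, and the follow-up analyses are exploratory.

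It is also fair to say that the size of the loss is undetermined. Selection at 35 weakens the T0–T1 correlation too (0.6 falls to 0.48 in the first row above). Nor does timing relative to treatment clearly separate the scores, because patients only scheduled for treatment may enter, so T0 may also precede treatment.

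Finally, the article condenses a longer protocol and cites a reference at this sentence, so the choice may have been deliberate. That would answer why screening was chosen. It would not remove the inconsistency with the design factor and the other ANCOVAs.

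**Conclusion.** The inconsistency is on the page: one covariate for the primary test, and another for the design factor and every other ANCOVA. The consequence is limited to efficiency and consistency. There is no bias, and the sample size of 219 and the planned 80% power are unaffected.

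Under the assumed correlations the screening score leaves about 1% to 17% more residual variance than T0. The low end applies if both scores correlate equally with T1 before selection and closely with each other. The high end applies if T0 correlates better by 0.1. The screening score was the weaker covariate in every scenario examined, but the documents cannot say by how much. Adjusting for T0 is a free improvement and does not repair an invalid analysis.

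**What to change.** In the primary ANCOVA, replace the CIS-fatigue screening score with the CIS-fatigue score at T0. The screening score may stay as an additional covariate. Use the same CIS-fatigue baseline at T1, T2 and T3. If the screening score is kept as the only covariate, state the reason and define the design-factor correlation as that between screening and T1.

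The cost is one phrase in Statistical analyses, fixed before the data are analysed. T0 CIS-fatigue is already scheduled for every participant before allocation, so no new data are needed and the sample size does not change.
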